### Withdrawal

Participants are considered withdrawn when consent is revoked. Withdrawn participants will not undertake any further assessment or intervention. Data collected up until point of withdrawal will form part of the study result. Participants will not be withdrawn if not adhering to protocol. Withdrawal from the trial will have no impact on the care offered to families.

### Data storage

All patient outcome measures will be collected in paper format and stored in a locked cabinet at Lady Cilento Children’s Hospital with restricted access. Data from wearable activity trackers are stored by Garmin (Garmin Ltd., Lenexa, KS, USA); participants will give the investigators permission to download that information to the University of Queensland servers for the use of Clinician Support System. Trial data will be stored electronically on a password protected Queensland Health Server for a period of 15 years in accordance with NHMRC guidelines. Data will be checked and cleaned prior to being locked for analysis.

### Data monitoring

The research team will meet every six months to ensure that recruitment is on schedule and performed ethically, as well as to assess any adverse events associated with the intervention. Any adverse events will be immediately notified to the overseeing ethics committee (Children’s Health Queensland) and the site-relevant governance committee, and the TSC. In occurrences where safety concern is identified by the research team, a suspension of the trial can be issued by the research team and a recommendation to the overseeing ethics and site governance committee to modify or stop the trial will be made.

### Treatment Fidelity

All treating physiotherapists involved in the trial will undergo a training session on the use of the eHAB®, Garmin Connect (Garmin Ltd., Lenexa, KS, USA), and Clinician Support System led by the research team. Handouts and manuals will be developed by the research team and easily accessible to the clinical team. The research team will be in clinic on a regular basis to maintain adherence to protocol.

## Discussion

To the best of the authors’ knowledge, this study is the first in the world to assess the efficacy of a telehealth-based outpatient physiotherapy clinic for children with CF. Emerging literature supports the efficacy of online telehealth clinics in offering increased access to care for adults with cystic fibrosis ([10]; Jamie [9]) and remote monitoring for deteriorating health [8]. In previous studies, researchers have examined each innovation independently as an alternative to current practices. In this study, researchers will utilise these innovations as an adjunct to existing services (Fig. 1). The new model of care will enable clinicians to better facilitate ongoing intervention programs in the future.

**Fig. 1 Fig1:**
[figure not shown]
Integration of CyFiT Intervention with current Model of Care

Remote monitoring of physical activity and health-related data is an essential part of the proposed model. Previously, activity diaries have been used to monitor physical activity, however these are self-reported and often inaccurate [28]. The use of wrist-worn activity trackers should alleviate such inaccuracies. Activity trackers continuously collect health-related data passively in near-real-time, which will provide more data. Consumer-based activity trackers have been chosen over clinical/research counterparts to increase acceptance from children in the trial.

The large amount of data that will be available for clinicians raises new challenges. The sheer volume of data from activity trackers have previously made near-real-time analysis impractical and unusable in a clinical setting. To minimise this, a clinician support system will be developed for this study to facilitate the near-real-time statistical modelling and display of information in a cost-effective manner.

Study bias has been minimised such that the research team and assessor are blinded from participant allocation and are not directly involved in the clinical management of participants.

Telehealth-based physiotherapy consultations enable children and physiotherapists to access more diverse and engaging options of therapeutic intervention. Telehealth enables online group sessions where multiple children can participate in a session together without the risk of cross infection. Social-based activities and gamification elements offered by consumer-based activity trackers may reinforce physical activity habits in children. Identifying practical means of continually engaging and facilitating children in participating in airway clearance and activities of daily living will yield long-term benefits for children with CF.

In conclusion CyFiT OPS is formulated around a patient-centred model. Establishing the clinical utility of CyFiT OPS means that families can receive the same quality of physiotherapy service closer to home, with a reduced risk of cross infection. This study will also supplement existing literature by providing high quality evidence regarding the use of telehealth in managing children with CF.

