### Randomisation

Children will be randomised via concealed random allocation. A computerised random number sequence will be generated that corresponds to the two study arms (1 = Usual OPS, 2 = CyFiT OPS) in balanced-blocks of eight participants (i.e. 4 Usual OPS, 4 CyFiT OPS). The result of each randomisation will be concealed inside a sequentially numbered, opaque envelope. Intervention will be provided to each child in one of two treatment arms: Usual OPS or CyFiT OPS. The allocation of each child will be recorded on an electronic, password protected spreadsheet that is unknown to the trial assessor, and then contents of the envelope will be discarded.

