#### CyFiT outpatient physiotherapy (CyFiT OPS)

Participants allocated to the CyFiT OPS group will receive OPS via telehealth as the primary mode of delivery. In this group, a different telehealth system called eHAB® will be used. The eHAB® system was developed at The University of Queensland for specialised telerehabilitation. When using eHAB® with an individual child, clinicians can access additional digital functions not available via existing QH Telehealth System, such as real-time image/video sharing, whiteboard for drawing diagrams, measurement tools for looking at various joint ranges of motion across the body and session recording that will facilitate an enhanced telehealth experience compared to videoconferencing alone. In addition, eHAB® enables clinicians to work with groups of children, for example to host real-time multipoint video conferences to deliver virtual group-based sessions.

In addition to having access to the eHAB® telehealth system for CyFit OPS, children allocated to the CyFiT group will be asked to wear a consumer-based wrist-worn activity tracker, Garmin Vivosmart3® (Garmin Ltd., Lenexa, KS, USA), during the 12-month intervention period. Children can utilise all functions available on the activity tracker. Health-related data (such as heart rate variability, sleep duration, steps, distance travelled, energy expenditure) will also be monitored by the treating team to inform physiotherapy practices in exercise prescription and in telehealth sessions (with access to near-real-time physiological information).

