##### Phase one

Phase one is an opportunity for children and clinical physiotherapists to familiarise themselves with technology (i.e. activity wristbands and eHAB®). During this period, children will only be participating in one-to-one OPS via telehealth in the intervention group as clinically indicated. Treating physiotherapists will have access to health-related data via supplier web portal. Health-related data collected during phase one will enable the research team to derive statistical models to monitor children’s health and better assist clinical decision making.

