### Blinding

The nature of this trial prevents the blinding of both the treating clinicians and patients. Both clinicians and patients will be exposed to the allocation via a) what modality they receive their physiotherapy service, and b) health-related data from activity trackers. Outcome measures will be collected by a blinded assessor. Randomisation will only occur after initial baseline assessment. Patients will always be approached by an unblinded clinical team prior to reassessment to mitigate risk of unblinding of the assessor (e.g. removing wristbands for the assessment).

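### The Discussion says the research team is blinded to allocation, but team members who handle the CyFiT-only tracker data cannot be

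*Protocol article*

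**What the plan says.** The claim is in the Discussion, in the text after Figure 1. Bias is said there to have been kept down because "the research team and assessor are blinded from participant allocation and are not directly involved in the clinical management of participants". The sentence covers two parties, the research team and the assessor, and does not limit which team members it means.

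The methods sections are narrower:

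- **Blinding.** Treating clinicians and patients cannot be blinded. Two routes of exposure are named: the mode in which physiotherapy is received, and the health data from the trackers. The protection stated is "Outcome measures will be collected by a blinded assessor". The research team is not mentioned.
- **Randomisation.** Allocations are kept on an "electronic, password protected spreadsheet that is unknown to the trial assessor". Nobody else is named as kept from it.
- **CyFiT outpatient physiotherapy.** "children allocated to the CyFiT group will be asked to wear a consumer-based wrist-worn activity tracker". The Usual OPS section provides for no tracker.
- **Phase one.** "Health-related data collected during phase one will enable the research team to derive statistical models to monitor children’s health".
- **Phase two.** Tracker data and a risk score are shown to physiotherapists in the clinician support system.
- **Data storage.** Participants permit the investigators to download the tracker data to university servers.

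**The concern.** Patients and clinicians know the arm, and the primary outcome is a questionnaire. In such a trial, two places remain where blinding can help: the collection of outcomes, and the choices made by those who prepare and analyse the data. The Discussion tells the reader that both are covered, since it names the research team alongside the assessor.

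If part of that team sees data that exist in one arm only, the second protection does not hold for those members. A reader, or an ethics committee, would then credit the trial with a safeguard that it does not have. Arm-aware choices in the analysis would also go unguarded, because the plan takes the people concerned to be blind already.

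**Working it through.** No arithmetic decides this point. The check sets the claim against the procedures.

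**Step 1. Does holding tracker data reveal the arm?** Yes. Trackers are part of the CyFiT intervention only, so a child with a tracker feed is a CyFiT child. The reverse is weaker: a child without a feed is probably in Usual OPS, but CyFiT children are only asked to wear the device and some may not. The Blinding section supports this step, because it names tracker data as one of the two ways in which clinicians and patients are exposed to allocation.

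**Step 2. Does the research team hold these data?** Yes. Phase one assigns the modelling to the research team by name, and Data storage gives the investigators permission to download.

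**Step 3. Does this happen while the trial runs?** Yes. The models come from data of months 0 to 6, and a risk score is to be displayed in months 6 to 12. The modelling therefore cannot wait until follow-up is complete. Assessments at 12 and 18 months still lie ahead for children then in phase two.

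**Step 4. Does any procedure separate the team from allocation?** None is stated. The spreadsheet is kept from the assessor only, and the Blinding section's measures, such as taking off wristbands before reassessment, also protect the assessor only. The article describes no coded tracker data and no division into blinded and unblinded research staff.

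**Step 5. What do the other team tasks add?** They are supporting inferences only.

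| Section | Task | What it shows |
|---|---|---|
| Data monitoring | The team meets six-monthly, "as well as to assess any adverse events associated with the intervention" | Hard to do without knowing the arm, but not said to be done by arm or by child |
| Treatment Fidelity | "The research team will be in clinic on a regular basis to maintain adherence to protocol" | The arms differ in mode of delivery, but disclosure of allocations is not stated |
| Medical record information | Chart review records face-to-face and telehealth appointments | A clue to the arm; who does the review is not stated |

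**Extent.** The planned CyFiT arm is 55 of 55 + 55 = 110 children. If all wear the tracker, 55/110 = 50% of participants are directly identifiable to those who handle the feed. The stated sample size does not depend on this point.

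**The case against.** The strongest reply is that this is one loose sentence in a Discussion. The Blinding section claims blinding for the assessor only and is open that clinicians and patients are not blinded. A full protocol may split the team or code the tracker data, and a journal article commonly leaves that out.

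Part of this stands. The methods sections make no false claim, and absence of detail on sub-teams would not be a finding in itself. But the Discussion sentence is a positive, unqualified statement, and it is the article's only statement on research-team blinding. If sub-teams exist, it is still wrong as written, because it does not say which staff it covers.

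A reader might infer several stronger things that the document does not support:

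- **That the trial has no effective blinding.** Assessor blinding has its own procedures in Randomisation and Blinding, and nothing here refutes them.
- **That an arm-aware team extracts the charts and runs the analysis.** Medical record information and Data analysis name nobody for these tasks. Cost effectiveness does have investigators estimate some patient costs, but from published figures such as fuel cost.
- **That appointment mode proves the arm.** Usual OPS may include telehealth, and in CyFiT telehealth is the primary mode, not stated to be the only one.
- **That adverse event review or clinic presence discloses allocation.** Neither section says so. Both arms attend the same face-to-face multidisciplinary clinics and are treated by the same physiotherapy team.
- **That the team takes part in clinical management.** The sentence's denial of direct involvement is not contradicted by these passages.

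**Conclusion.** The point holds in a limited form. The claim that the research team is blinded is contradicted by the protocol's own procedures for those team members who handle tracker data. That part rests on explicit text in five places: the CyFiT intervention, Phase one, Data storage, Blinding and Randomisation.

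It rests on two assumptions. The first is that the tracker data seen by the team can be linked to trial participants; the article describes no coding that would prevent it. The second, needed only for the download route, is that the investigators belong to the research team. The Phase one text names the team directly and does not need it.

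Up to 55 of 110 children are identifiable in this way. The direction and size of any bias in the CFQ-R or other outcomes cannot be derived from the article, and collection of the CFQ-R by the blinded assessor is not shown to be affected. The trial is not invalidated. A stated bias safeguard is inaccurate and cheap to correct, so it should be corrected.

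**What to change.** 1. **Discussion.** Limit the blinding claim to the outcome assessor.
2. **Blinding.** Add that research team members with access to tracker data or to allocation are not blinded. If some members, such as the analyst, are to stay blind, name the role and say how it is kept from both.
3. **Analysis.** Run the CFQ-R comparison under dummy arm codes until the analysis code is locked, where possible by an existing team member who does not handle tracker data. The non-inferiority question has a direction, so the locked code should report the confidence interval for arm A minus arm B. The non-inferiority reading is then made once the codes are opened.

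The cost is wording, one small coding step at analysis, and a blinding statement that looks less favourable. No visits are added and the sample size does not change. There are two limits. The article does not say whether a team member without tracker access exists. Dummy codes at analysis also do not blind whoever extracts the charts.

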## Abbreviations

CAPE: Children’s Assessment of Participation and Enjoyment
CF: Cystic Fibrosis
CFQ-R: Cystic Fibrosis Questionnaire – Revised
CHQ-HHS: Children’s Health Queensland Hospital and Health Services
FEF_25–75_: Forced Expiratory Flow at 25–75%
FEV1: Forced Vital Volume in One Second
FEV1/FVC: Forced Vital Volume in One Second divided by Forced Vital Capacity
LCCH: Lady Cilento Children’s Hospital
MCID: Minimal Clinical Important Difference
MDT: Multi-disciplinary Team
MPOC: Measure of Processes of Care
MST25: Modified Shuttle Test with 25 levels
NHMRC: National Health and Medical Research Council (Australia)
OPS: Outpatient Physiotherapy Service
PAC: Preferences of Activity of Children Questionnaire
QH: Queensland Health
